### Treatment fidelity

Regarding assessing treatment fidelity, our strategy is to ensure that tapes from each practitioner are sampled to establish that each treatment arm is being delivered according to the specified standard. The procedures for assessing treatment fidelity will be identical for both interventions. The description here applies to each intervention arm. The raters for the two interventions will be independent to minimise contamination.
*Stage 1 (Calibration)*: A sample of five tapes (one from five practitioners selected at random) for each intervention will be rated by national experts to provide a target rating to be used in the training and standardisation of subsequent ratings. The national rater(s) for CfD will be based at the University of York St John and for CBT at the Oxford Cognitive Therapy Centre (OCTC).
*Stage 2 (Independent fidelity ratings)*: Digital recordings of sessions will be selected at random using the following procedure. At the therapist level, for each therapist, one case will be selected at random per block of five seen cases (or upwards of 5). Hence, the sampling strategy ensures that (1) all therapists are sampled and (2) the pool of rated tapes and overall competence ratings reflect the differential loading carried by therapists. At the session level, for each case sampled, the selected session will be randomly selected from early (excluding session 1), middle or late (excluding final session). This sampling strategy will yield a total of 50 tapes per intervention, thereby providing a total of approximately 100 tapes to be rated in the trial (although the actual number may vary as a function of numbers of therapists and the number of sessions delivered).
*Stage 3 (Independent fidelity audit)*: As a final check, a small subsample of the independent fidelity ratings will be audited by experts in the respective therapies.

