**Methods:**

PRaCTICED is a two-arm, parallel group, non-inferiority randomised controlled trial comparing CfD against CBT. It is embedded within the local IAPT service using a stepped care service delivery model where CBT and CfD are routinely offered at step 3. Trial inclusion criteria comprise patients aged 18 years or over, wishing to work on their depression, judged to require a step 3 intervention, and meeting an ICD-10 diagnosis of moderate or severe depression. Patients are randomised using a centralised, web-based system to CfD or CBT with each treatment being delivered up to a maximum 20 sessions. Both interventions are manualised with treatment fidelity tested via supervision and random sampling of sessions using adherence/competency scales. The primary outcome measure is the Patient Health Questionnaire-9 collected at baseline, 6 and 12 months. Secondary outcome measures tap depression, generic psychological distress, anxiety, functioning and quality of life. Cost-effectiveness is determined by a patient service receipt questionnaire. Exit interviews are conducted with patients by research assessors blind to treatment allocation. The trial requires 500 patients (250 per arm) to test the non-inferiority hypothesis of −2 PHQ-9 points at the one-sided, 2.5% significance level with 90% power, assuming no underlying difference and a standard deviation of 6.9. The primary analysis will be undertaken on all patients randomised (intent to treat) alongside per-protocol and complier-average causal effect analyses as recommended by the extension to the CONSORT statement for non-inferiority trials.

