Prior to the trial commencing, we provided CfD training to all counsellors in Sheffield IAPT that has facilitated a move towards standardised practice and evidence-based service evaluation. CfD training standardises counselling work with depressed patients and aligns therapist interventions with the evidence-base underpinning NICE guidelines. The CfD training is aimed at experienced person-centred and humanistic practitioners as a ‘top-up’ provision. The training consisted of a 5-day taught programme delivered across a 1 or 2-week block, followed by a period of supervised clinical work. During clinical practice associated with CfD training, a minimum of 80 h of supervised practice must be completed. Only those who have completed the training will be included within the trial, meaning increasing numbers of counsellors will be included as the trial progresses. The delivery of CfD is standardised by adoption of the text *Counselling for depression: A person-centred and experiential approach to practice* [25]. Manuals based on this text, the CfD theoretical approach and training have been developed and provided to all counsellors to act as an on-going reference and training resource [26].

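### The Stage 2 fidelity sampling rule does not ensure that every therapist is sampled, because a therapist with one to four trial cases yields no tape

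*Protocol article*

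**What the plan says.** The Treatment fidelity section of the protocol article gives its aim at the outset: "our strategy is to ensure that tapes from each practitioner are sampled". Stage 2 then sets the rule for each therapist: "one case will be selected at random per block of five seen cases (or upwards of 5". Two properties are claimed for it. The first is that "the sampling strategy ensures that (1) all therapists are sampled"; the second is that the pool of tapes reflects how the workload is spread over therapists. The expected yield is given next: "This sampling strategy will yield a total of 50 tapes per intervention", about 100 in all, with the caveat that "the actual number may vary as a function of numbers of therapists and the number of sessions delivered".

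Three other places bear on the point. The section on CfD admits only counsellors who have completed training, "meaning increasing numbers of counsellors will be included as the trial progresses". The Discussion hopes for about 30 therapists in total and says that training counsellors has been slow in a largely part-time profession. The section on clinical supervision provides short supervisor ratings at sessions 2, 6 and 12, covering all trial patients.

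**The concern.** The plan presents coverage of every therapist as a consequence of the rule. It is a consequence only if every therapist reaches five trial cases, or if an incomplete block also counts, and the article states neither condition. A counsellor who qualifies late and sees three trial patients would contribute to the outcome data but have no independently rated session.

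Fidelity carries weight in this design. The Primary analysis section itself explains that therapy not delivered as planned pulls the arms together and can make CfD look non-inferior when it is not. Independent ratings are a main safeguard against that, and their value depends on covering all the therapists who treated patients. The same section makes therapist adherence one of the items reviewed for PP2, so a gap in the ratings would reach PP2 if these ratings are what the review uses.

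**Working it through.** **Inputs.** The sampling rule and the 50 tapes per arm come from Treatment fidelity. The 250 patients per arm come from the Abstract, and the 275 to be recruited per arm from Sample Size. The total of about 30 therapists comes from the Discussion; an even split of 15 per arm is my assumption. The documents give no caseloads, so every caseload pattern below is also an assumption.

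**Step 1, the plan's own figure.** Tapes per arm = cases per arm / 5 = 250 / 5 = 50, as stated. With 275 cases it would be 275 / 5 = 55. Under a full-block rule, division by five is exact only if every therapist's caseload is a multiple of five.

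**Step 2, the rule for one therapist with x cases.**
- Full blocks only: tapes = floor(x / 5). For x = 1, 2, 3 or 4 this is 0; for x = 5 it is 1.
- Incomplete blocks also count: tapes = ceil(x / 5). For x = 1 to 4 this is 1.

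Coverage of all therapists is therefore guaranteed under the second reading but not the first. The text describes blocks of five or more and never says that a smaller block counts.

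**Step 3, a worked example.** Take 15 therapists with caseloads 30, 30, 25, 25, 25, 20, 20, 20, 15, 15, 11, 6, 4, 3, 1 (total 250).
- Full blocks: 6+6+5+5+5+4+4+4+3+3+2+1+0+0+0 = 48 tapes. Three therapists have none; they hold 4+3+1 = 8 of the 250 cases (3.2%).
- Incomplete blocks counted: 6+6+5+5+5+4+4+4+3+3+3+2+1+1+1 = 53 tapes, and every therapist has at least one.

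**Step 4, how often this could arise.** The mean caseload is 250 / 15 = 16.7 (275 / 15 = 18.3), so a typical therapist is sampled about three times. What matters is the lower tail. Cases were allocated at random to 15 therapists in one arm, 3,000 times per pattern. Each cell gives the mean number of therapists with one to four cases, then the probability of at least one.

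| Assumed caseload pattern | 250 cases | 275 cases |
|---|---|---|
| Equal expected loads | 0.0; 0.003 | 0.0; 0.000 |
| Loads falling linearly with order of entry | 1.88; 0.948 | 1.73; 0.936 |
| Randomly uneven (Dirichlet, parameter 2) | 1.63; 0.854 | 1.41; 0.802 |
| Randomly uneven (Dirichlet, parameter 1) | 2.85; 0.968 | 2.61; 0.953 |

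In the linear pattern the weights run from 14.5 down to 0.5 and sum to 112.5. The last two entrants therefore expect 250 × 0.5 / 112.5 = 1.1 and 250 × 1.5 / 112.5 = 3.3 cases.

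**Step 5, total yield with 15 therapists.** Full blocks give about 44 tapes per arm from 250 cases and about 49 from 275. Counting incomplete blocks gives about 56 and 61.

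**The case against.** The best defence is that the rule is loosely worded rather than wrong. The section opens with the aim of sampling every practitioner and applies the rule therapist by therapist. The phrase about five or upwards is unclear, and the article condenses a fuller protocol. If incomplete blocks were meant to count, or if every therapist reaches five cases, all are sampled. This stands as a limit on the point: the rule fails to ensure coverage, which is different from being unable to achieve it. It does not rescue the claim, because the article draws the guarantee from the rule as written.

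The independent ratings are also not the only evidence on delivery. Supervisors complete adherence and competence forms for all patients, including those of low-volume therapists. That softens the consequence, but these are simplified four-item ratings by the supervisor and not independent. Nor do the other stages close the gap: Stage 1 rates one tape from each of five randomly chosen practitioners per arm, and Stage 3 audits a subsample of Stage 2.

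Three stronger readings are tempting, and the documents do not support them.
- *The plan will fall short of 50 tapes.* The protocol says the number may vary. With the 275 patients per arm it plans to recruit, full blocks alone give about 49 if all are seen.
- *A definite number of therapists, in particular the latest to join, will be missed.* A late joiner is missed only by finishing below five cases. The counts in the table rest on assumed caseloads and fall to zero when expected loads are equal.
- *The fidelity estimate is biased upward, and unequally between arms.* Nothing in the protocol shows that newer or less-used therapists deliver worse, and counsellors must complete 80 supervised hours and a final tape assessment of competency.

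**Conclusion.** The point holds in a limited form and is minor. On its plain wording, the rule does not deliver the coverage that the protocol says it ensures: any therapist ending with one to four trial cases yields no tape. Staggered entry makes this plausible in the CfD arm. With 15 therapists per arm, the number missed runs from about zero to about three across the caseload patterns tried; that range illustrates the assumptions and does not estimate what will happen. The consequence is limited to the independent fidelity description, and to PP2 if its case review draws on these ratings. The primary intention-to-treat analysis, the non-inferiority margin and the sample size do not depend on it.

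**What to change.** Replace the Stage 2 rule with one that makes the stated property true. Select at least one case at random from every therapist who saw any trial patient, then allocate the remaining tapes to therapists in proportion to caseload, keeping the planned total of about 50 per arm. With 15 therapists in an arm, that is 15 tapes for coverage and 50 − 15 = 35 shared by caseload. Weight the overall fidelity summary by caseload so that it describes the therapy that patients received.

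Stage 2 excludes the first and final sessions. If none of a therapist's cases has an eligible session, report that therapist as unrated.

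The change adds no rating work while the total stays at 50. Its only downside is slight over-representation of low-volume therapists among the tapes, which the weighting removes. The article reports recruitment as ongoing, so the rule could be amended before the fidelity results are reported.

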### Patient consent process

PWPs are the initial point of contact and gatekeepers for entry into the trial (i.e., there is no direct GP referral or self-referral into the trial). PWPs utilise both face-to-face as well as telephone assessments of patients in their work. If the PWP considers that, during their initial assessment of the patient or their subsequent work with them, the trial would be an appropriate course of treatment, then they introduce the trial and request consent for the research team to contact them. Appropriateness for the trial is that a patient’s PHQ-9 score is 12 or higher and that they present with depression and wish to be treated for depression. Ethics approval has also been given for this procedure to be carried out over the telephone. Potential participants are then sent information on the trial and a Consent to Treatment form together with an appointment date for an assessment interview.

The PWP contacts the patient 2–4 days before the screening appointment to answer any questions about the trial and check that the patient is still willing to attend the screening. Should the patient not wish to proceed with the trial, the PWP will carry out the usual procedures for non-trial patients. At the screening appointment, the patient has the opportunity to ask any further questions before signing consent forms to enter the trial. They are also provided with contact information and consent to be contacted by researchers in the future.

### Diagnostic assessment

Patients attending the assessment interview are asked again whether they have a strong preference for one or the other treatment such that they would refuse a treatment if it were offered to them. The primary measure for determining suitability for the trial is the Clinical Interview Schedule-Revised (CIS-R) with the requirement that patients meet an ICD-10 diagnosis of moderate or severe depression [16]. Assessment interviews are carried out either by Clinical Support Officers (CSOs) or members of the research team. All assessors are trained in using the CIS-R. If active thoughts of suicide are indicated from the CIS-R, we implement a risk protocol to inform the PWP or identified practitioner. In terms of alcohol or substance dependency, these are determined by specific questions from Section I (Alcohol) and Section II (Drug) of the Mini-International Neuropsychiatric Interview (M.I.N.I.) [36], which yield diagnoses of current alcohol or drug dependency. If a patient meets an ICD-10 diagnosis of moderate or severe depression, they are consented into the trial. Patients who do not meet the criterion are talked through the reasons and referred back to the PWP. Figure 1 presents a flow study chart of the progress of patients through the trial.

**Fig. 1 Fig1:**
[figure not shown]
Study flow diagram of referral, screening and allocation of patients to the PRaCTICED trial. Legend: *BDI-II* Beck Depression Inventory II, *CSQ* Client Satisfaction Questionnaire, *CD-RISC* Connor-Davidson Resilience Scale, *CIS-R* Clinical Interview Schedule-Revised, *CSRI* Client Service Receipt Inventory, *CORE-OM* Clinical Outcomes in Routine Evaluation-Outcome Measure, *EQ-5D-5L* Euroqol 5D-5L, *GAD-7* Generalised Anxiety Disorder-7, *MINI* Mini International Neuropsychiatric Interview, *PHQ-9* Patient Health Questionnaire-9, *QoLS* Quality of Life Scale, *WSAS*, Work and Social Adjustment Scale

### Randomisation

Consenting patients are allocated to one of the two treatment arms via remote access to the randomisation procedure that is hosted by epiGenesys, a wholly owned subsidiary of the University of Sheffield.

### Blinding

Allocation to either intervention is recorded in a separate location in the patient data log. The assessors carrying out the therapy exit interviews do not have immediate access to information regarding allocation assignment. Statisticians conducting the analysis will not be involved in the administration of the trial and will be blinded to the randomisation. Key variables (i.e., treatment assignment) will be coded as non-identifiable variables to minimise potential biasing in analyses. Blinding of a patient’s assignment to treatment will only be unmasked on the specific direction of the Data Management and Ethics Committee.

### Measures

Patients then complete the second part of the assessment interview comprising the completion of a battery of measures. All assessors receive a standard training regarding the collection of assessment data. A summary of the assessments is presented in Fig. 2.

**Fig. 2 Fig2:**
[figure not shown]
SPIRIT diagram of assessments at enrolment, allocation, weekly sessions, and 6- and 12-month time points Legend: *BDI-II* Beck Depression Inventory II, *CD-RISC* Connor-Davidson Resilience Scale, *CIS-R* Clinical Interview Schedule-Revised, *CSRI* Client Service Receipt Inventory, *CSQ* Client Satisfaction Questionnaire, *CORE-OM* Clinical Outcomes in Routine Evaluation-Outcome Measure, *EQ-5D-5L* Euroqol 5D-5L, *GAD-7* Generalised Anxiety Disorder-7, *MINI* Mini International Neuropsychiatric Interview, *PHQ-9* Patient Health Questionnaire-9, *QoLS* Quality of Life Scale, *WSAS*, Work and Social Adjustment Scale

#### Treatment Preferences and Credibility

Patient preferences and credibility regarding the two interventions are measured using standard scales adapted to the specific interventions [37, 38].

#### Primary Outcome

##### Patient Health Questionnaire-9 (PHQ-9) [39]

The primary outcome measure is the PHQ-9, a brief (9-item) self-report 4-point Likert-type scale measure of depression. Items correspond to each of the nine DSM-5 criteria for depression [40]. Items ask patients to rate how often they have been affected by symptoms (of depression) over a 2-week time period prior to completing the questionnaire.

Individual item scores range from 0 (*“not at all”*) to 3 (*“Nearly every day”*) with total PHQ-9 scores ranging from 0 to 27. Scores of 10 and above are demarcated as clinical scores. Scores of 5–9, 10–14, 15–19 and 20–27 are classified as reflecting mild, moderate, moderately severe and severe levels of depression respectively. The measure has an internal reliability of 0.89 and a test-retest reliability of 0.84 across 48 h. The PHQ-9 is mandated by the IAPT service and is completed by patients at each session attended along with other mandated measures within the IAPT minimum data set (MDS) [41].

#### Secondary Outcome Measures

A range of secondary outcome measures is collected. At baseline, the intensity of depression is measured via the Beck Depression Inventory-II (BDI–II) [42], psychological distress via the Clinical Outcomes in Routine Evaluation-Outcome Measure (CORE-OM) [43], generalised anxiety via the Generalised Anxiety Disorder Assessment (GAD-7) [44], plus the Work and Social Adjustment Scale (WSAS) [45]. Mobility, self-care, usual activities, pain/discomfort and anxiety/depression are measured via the EQ-5D-5L [46, 47] and Quality of Life Visual Analogue Scale (QoLS) (personal communication: [name]). In addition, patients complete the Connor-Davidson Resilience Scale (CD-RISC) [48]. Patient service receipt data are also collected [49]. At 6- and 12-month follow-ups, in addition to the PHQ-9 as the primary outcome, the BDI-II, CORE-OM, GAD-7, WSAS, EQ-5D-5L, QoL and CSRI are collected, as is the Client Satisfaction Questionnaire (CSQ) [50].

Four weeks after a patient ends treatment, either through completing or dropping out from sessions, they are contacted to undertake a brief questionnaire/short interview (telephone, face-to-face or web-based) to collect data on their experiences of the treatments.

### Sample Size

Published findings [2–4] and Sheffield IAPT service data (1/4/09 – 30/9/10) indicate only small differences in outcomes between CBT and counselling. Hence, from these findings we predict the actual difference in mean change between treatments to be zero. Accordingly, the margin within which CBT could not be considered statistically or clinically more effective than CfD was determined as follows: First, treatment effects of 0.2 to 0.3 are conventionally viewed as ‘small’ and of limited clinical value (e.g., [51, 52]). Second, it has been recommended that the threshold for non-inferiority be set at 50% or less than the expected difference between CBT and usual care, which would mean an effect size of less than 0.3 (i.e., 0.6/2). Finally, discussions with psychologists on the research team and IAPT staff indicated that less than 2 points on the PHQ-9 is not perceived as clinically important, which is equivalent to an effect size of just under 0.3 (given the pre-last SD of 6.9 found in the service data above). Therefore, a pre-last change difference of less than 2 on PHQ-9 in favour of CBT was adopted as the limit for non-inferiority of CfD.

It is estimated that 550 patients (275 per arm) would need to be recruited to the trial to secure the 500 patients needed to test the non-inferiority hypothesis at the one-sided 2.5% significance level with a power of 90%. This assumes a standard deviation of 6.9 (derived from the aforementioned service use data, which incorporate both inter-patient and inter-therapist variability), no underlying difference between the effect of CBT and counselling and a 10% loss to 6-month follow-up. As the trial is within a service with few additions to routine practices and procedures, it is expected that relatively few participants will leave the trial and not provide a 6-month follow-up PHQ-9. To sustain adequate referrals via PWPs, weekly monitoring of referral rates in each sector occurs together with monthly feedback via sector managers as well as target setting.

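### Minor: at the stated 10% loss, recruiting 550 leaves 495 patients with 6-month data, not 500; the effect on power is negligible

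*Protocol article*

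**What the plan says.** The Sample Size section of the protocol article gives the target as follows: "It is estimated that 550 patients (275 per arm) would need to be recruited to the trial to secure the 500 patients needed". The 500 are those needed for 90% power at the one-sided 2.5% level. The same paragraph lists the assumptions: "This assumes a standard deviation of 6.9", together with "no underlying difference between the effect of CBT and counselling and a 10% loss to 6-month follow-up". The margin is set just before: "a pre-last change difference of less than 2 on PHQ-9 in favour of CBT was adopted as the limit for non-inferiority of CfD". The Methods part of the abstract repeats 500 (250 per arm) with the same error rate, power, margin and SD, but gives no recruitment figure or loss rate.

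Two other places bear on the point. The abstract and the Primary analysis section make the analysis of all randomised patients primary. The Missing data section relies first on recruiting enough patients to cover dropout, and then on imputation that draws on PHQ-9 scores from attended sessions when the 6-month score is missing.

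**The concern.** The paragraph fixes three numbers: 550 recruited, 10% lost, 500 retained. Any two of them determine the third, and these three do not agree. A loss rate applies to the patients who were recruited, so the inflation is a division by 0.90; the printed target is what multiplication by 1.10 gives.

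What is at stake is the accuracy of the recruitment target. Readers will use that figure to judge whether the trial reached its planned size, and the Missing data section names recruitment to cover dropout as its first safeguard. The effect on power has to be worked out before anyone reads more into the slip.

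**Working it through.** **Inputs, all from the Sample Size section:** SD 6.9; margin 2 PHQ-9 points; true difference 0; one-sided α 0.025 (z = 1.960); power 90% (z = 1.2816); loss 10%; 500 needed; 550 recruited. The abstract confirms 250 per arm.

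**1. The plan's own figure for patients needed.**
n per arm = 2 × SD² × (1.960 + 1.2816)² / margin² = 2 × 6.9² × (3.2416)² / 2² = 250.13.
This reproduces the stated 250 per arm, 500 in total. Strict rounding up would give 251 per arm, 502 in total; the difference is trivial.

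**2. The recruitment target.**
- 500 × 1.10 = 550, which is the printed figure exactly. The article does not show its calculation, so this route is inferred from the match.
- 500 / (1 − 0.10) = 555.6, so 556 in total; 250 / 0.90 = 277.8, so 278 per arm.
- Difference: 6 recruits, 1.1% of 556.

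**3. What 550 retains.**
- At 10% loss: 550 × 0.90 = 495, or 247.5 per arm on average, which is 5 fewer than 500.
- Loss at which 550 gives 500: 1 − 500/550 = 9.1%.

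**4. Effect on power, complete cases only.**
Power = Φ( margin / (SD × √(2/n)) − 1.960 ).

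| Patients with 6-month data | n per arm | Normal approximation | Noncentral t |
|---|---|---|---|
| 500 | 250 | 89.99% | 89.87% |
| 495 | 247.5 | 89.70% | 89.58% |

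The loss of power is about 0.3 percentage points by either method.

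**5. Scale against the precision of the inputs.** The SD is given to one decimal, so 6.9 could stand for anything from 6.85 to 6.95. Scaling the result of step 1:
- SD 6.85: 250.13 × (6.85/6.9)² = 246.5 per arm, about 493 in total.
- SD 6.95: 250.13 × (6.95/6.9)² = 253.8 per arm, about 508 in total.

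Rounding of the SD alone moves the required total by about 7 either way, more than the 5 patients in question.

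**The case against.** The strongest case for leaving the text alone is that nothing turns on it. The target is worded as an estimate, the section expects few patients to lack a 6-month PHQ-9, and 550 is sufficient at 9.1% loss, less than one percentage point below the round planning figure. The shortfall is smaller than the rounding of the SD, and power still rounds to 90%. The primary analysis covers everyone randomised, with session scores feeding the imputation, so a patient without a 6-month score need not contribute nothing. The 89.7% is therefore a pessimistic, complete-case figure.

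All of this stands as an argument about size, and it is why the point is minor. It does not make the three numbers agree. The estimate lies in the loss rate; once 500 and "a 10% loss to 6-month follow-up" are fixed, the recruitment figure follows by calculation. The expectation of low loss comes with no other rate. The sample-size paragraph takes no credit for imputation.

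A reader might go the other way and infer that the trial does not deliver its stated power, or that there is no slack to absorb the slip because 250 per arm already sits at 89.99%. The documents do not support either reading. Power at 495 agrees with 90% to the precision stated, and the complete-case calculation leaves out the information that the planned imputation would recover.

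**Conclusion.** Wrong as written, and minor. At the stated loss the target falls 5 patients short of 500 with 6-month data; equivalently, it is 6 recruits below the figure that matches 500 and 10%. The cost is about 0.3 points of complete-case power, from 89.99% to 89.7%, and imputation may make it smaller.

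This rests on the plan's own SD, margin, error rate and zero true difference, on independent observations with equal arms, and on loss counted as a share of those recruited. The slip gives no ground for saying that the trial is underpowered or that its non-inferiority conclusion is at risk.

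**What to change.** Restate the sentence in the Sample Size section and leave the target where it is. Suggested wording: 550 recruited (275 per arm) allows for a loss of up to 9.1% to the 6-month follow-up; at 10% loss 495 patients remain, with about 89.7% power before any gain from imputation.

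If the sponsor prefers to keep both 500 and 10% as stated, the recruitment figure that matches them is 556 (278 per arm).

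The first option costs one sentence and a marginally less round power figure. It needs no further enrolment and leaves the margin, the analysis and the 500 in the abstract unchanged.

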## Discussion

The PRaCTICED trial is a large-scale (and may be the only) randomised trial investigating the efficacy of CfD against CBT. Extensive evidence exists for the efficacy of CBT but the evidence for other psychological therapies lags behind. Determining the relative efficacy of other bona fide therapies is important for all stakeholders. The non-inferiority design adopts a realistic approach to such a comparison in the context of a pragmatic trial nested within an existing NHS IAPT service. Advantages of an embedded trial include having access to routinely collected outcome measures as well as the additional measures required specifically by the trial. The routinely collected data include weekly-administered outcome measures, including the primary outcome measure (PHQ-9). Not only does this increase the likely response rate in terms of the primary outcome, but it also provides the additional level of repeated weekly measurement on the primary outcome measure across the course of treatment. Hence, the data collection demand on trial patients is only proportionately greater than for non-trial patients receiving therapies within the routine IAPT service. Further additional advantages of the trial utilising a routine service lies in having access to larger number of therapists. While the exact total number will not be known until the trial is completed, the aspiration is to have in the region of 30 therapists in total delivering interventions in the trial. As such, this will provide a minimum level in order to be able to investigate therapist effects.

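### The stated 90% power makes no allowance for clustering by therapist: an SD that contains therapist variance does not supply one, so 90% holds only if the therapist ICC is close to zero

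*Protocol article*

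**What the plan says.** The Sample Size section sets the margin: "a pre-last change difference of less than 2 on PHQ-9 in favour of CBT was adopted as the limit for non-inferiority of CfD". It then gives 500 patients as the number needed for 90% power at the one-sided 2.5% level, with no true difference between treatments and 10% loss to 6-month follow-up. On variability it says "This assumes a standard deviation of 6.9", and describes that figure as "derived from the aforementioned service use data, which incorporate both inter-patient and inter-therapist variability". The SD comes from the Sheffield service data reported under Pilot work and determining type of trial.

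The abstract's Methods paragraph repeats the power claim, "at the one-sided, 2.5% significance level with 90% power, assuming no underlying difference and a standard deviation of 6.9", for 250 patients per arm, and says nothing about therapists.

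On therapist numbers, the Discussion says that "the aspiration is to have in the region of 30 therapists in total delivering interventions in the trial" and that this is a minimum for studying therapist effects. The article states no ICC, caseload or design effect.

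**The concern.** The remark about inter-therapist variability is the only place where the sample size calculation deals with therapists, and it reads as though it settles the matter. It does not. A total SD that contains both sources of variation describes how far one patient's change score lies from the mean. The precision of an arm mean also depends on how patients are grouped, because patients of the same therapist share that therapist's effect and so carry less independent information.

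The grouping matters for the treatment comparison. The sections on the two interventions, on training and on supervision describe CfD counsellors and CBT practitioners as separate groups with separate training, supervision and rating scales. Therapists are therefore in effect nested within arm, and their effects do not cancel in the difference between CfD and CBT.

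At stake is the headline power figure. A non-inferiority trial with less power than stated is more likely to end without a conclusion even if the treatments are equally effective.

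**Working it through.** **Inputs from the protocol article.** Margin 2 PHQ-9 points, SD 6.9, true difference 0, one-sided 2.5%, power 90%, 250 analysable patients per arm (Sample Size; abstract). About 30 therapists in total (Discussion).

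**Assumptions, not in the documents.** Therapists split 15/15; equal caloads of m = 250/15 = 16.7 patients; ICC from 0.01 to 0.05.

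**Step 1: reproduce the stated size.** For independent patients, n per arm = 2 × (1.96 + 1.2816)² × 6.9² / 2² = 250.1. In the other direction, SE = 6.9 × √(2/250) = 0.617, and power = Φ(2/0.617 − 1.96) = 90.0%. The plan's figure is reproduced with a design effect (DE) of 1.00, so nothing has been added for clustering.

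**Step 2: what a total SD leaves out.** Let SD² = between-therapist variance + within-therapist variance, and ICC = between-therapist variance / SD². With equal caseloads the variance of an arm mean is (SD²/n) × [1 + (m − 1) × ICC]. Using the total SD supplies SD²/n only. The bracket equals 1 only if the ICC is zero or each therapist sees one patient.

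**Step 3: power when the analysis accounts for therapist.** DE = 1 + 15.67 × ICC, and power = Φ(2/(0.617 × √DE) − 1.96). The last column uses a t reference with 28 degrees of freedom (30 therapists minus 2 arms).

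| ICC | DE | Power, normal | Power, 28 df |
|---|---|---|---|
| 0 | 1.00 | 90.0% | 87.9% |
| 0.01 | 1.16 | 85.4% | 82.9% |
| 0.02 | 1.31 | 80.7% | 77.9% |
| 0.05 | 1.78 | 68.0% | 64.9% |

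A simulation of therapists nested in arm, analysed by therapist means (20,000 runs), gave 82.8%, 77.6% and 65.3% at ICC 0.01, 0.02 and 0.05, in line with the last column. By the normal approximation, power passes below 88% at an ICC of about 0.005.

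**Step 4: sensitivity to the assumptions (normal approximation).**
- 10 therapists per arm: 82.9% at ICC 0.01 and 58.9% at 0.05.
- 20 per arm: 86.6% and 73.3%.
- 15 per arm with unequal caseloads (coefficient of variation 0.5): 84.1% and 63.2%.

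**Step 5: the alternative case, an analysis that ignores therapist.** One-sided error at the margin = Φ(−1.96/√DE), which is 3.4%, 4.4% and 7.1% at ICC 0.01, 0.02 and 0.05 instead of 2.5%. The simulation gave 3.5%, 4.4% and 7.2%. Simulated power was then 88.0%, 86.7% and 83.3%. These figures replace those in Step 3; they do not add to them.

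**The case against.** **The ICC is unknown.** This stands as a limit on size. No ICC is given, and below about 0.005 the loss is under 2 points. Thirty therapists is an aspiration, the 15/15 split is assumed, and patients who never start therapy would lower the average caseload. A reader might infer that the design certainly falls well short of 90%; the documents do not support a categorical statement, nor ICC values much above the range used here. What does not depend on the ICC is that the stated rationale omits the factor.

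**The remark about the SD is literally true.** It is: the service data do contain both sources of variation, and the sentence does not claim a clustering adjustment in so many words. But it is the calculation's only reference to therapists, and the calculation contains no other allowance. The abstract gives only the SD and the power, so it carries the figure but not the rationale.

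**The SAP may model therapist.** It may. The Primary analysis section defers to it, the pilot section reports multilevel modelling of data from the same service, and the Discussion plans to study therapist effects. A reader might infer that the trial will claim non-inferiority falsely at more than 2.5%. The article nowhere says that the primary confidence interval will ignore therapist, so this remains a conditional risk. Nor can the inflated error be added to the full power loss, since each assumes a different analysis. Modelling therapist would protect the error rate but would not restore the stated power.

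**Baseline adjustment may help.** The 6.9 is the SD of unadjusted change, so adjustment could reduce it. To offset ICC 0.02 it would have to fall to about 6.9/√1.31 = 6.0. The article claims no such gain, so this is a possible partial offset that cannot be confirmed here.

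**Conclusion.** The point holds as a correction to the stated power and its justification. The 500 patients and 90% rest on independent patients, and including therapist variance in the SD does not change that. With therapists in effect nested within arm, 90% is right only at a near-zero ICC. If therapists number 15 per arm with equal caseloads and the analysis accounts for them, power is about 85%, 81% and 68% at ICC 0.01, 0.02 and 0.05, or about 83%, 78% and 65% with 28 degrees of freedom. The algebra and the reproduction of 250 per arm are certain; the size of the shortfall is conditional on an assumed ICC and assumed therapist numbers. Nothing in the documents shows that the primary analysis itself is at fault.

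**What to change.** In the Sample Size section, state that the SD of 6.9 is a total SD and does not adjust for clustering by therapist. There and in the abstract, replace the single 90% with a range tied to stated assumptions: for example, about 30 therapists split equally, with power of about 85%, 81% and 68% at ICC 0.01, 0.02 and 0.05, and 90% only if the ICC is negligible. If baseline adjustment is planned and is expected to reduce the SD, say so and by how much. The recruitment target need not change.

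Separately, confirm that the primary confidence interval in the SAP accounts for therapist. If it already does, nothing more is needed on that side.

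The cost is a wording change and a less favourable stated power. The restatement recovers no power; it lets readers judge an inconclusive result against the precision that the design can offer.
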